### Ethical Considerations

The study was approved by the scientific committee of the Jaslok Hospital and Research Centre (vide letter dated February 18, 2023; reference: -EC/1156/2023; Amendment 1). It was further approved by the ethics committee of Jaslok Hospital (vide letter dated February 18, 2023). It was also registered with Clinical Trials Registry India (dated March 27, 2023; CTRI/2023/03/051064). All participants provided informed consent (Multimedia Appendix 1). All data will be anonymized. The participants were provided travel compensation ($200 US per participant).

### Expected Outcomes

Participants in the intervention group are anticipated to show significant improvements in both motor and nonmotor aspects of PD. Improvements in gait and balance are expected, alongside positive changes in QoL, mood, cognition, and behavior. Caregivers of participants in the intervention group are also likely to report an enhanced QoL due to the improved condition and mood of the patients they care for.

## Results

The data collection for this paper commenced in February 2023 and was completed in February 2024. A total of 30 participants were recruited, of which 28 completed the study (intervention group: n=15, 54% and control group: n=13, 46%). The data are currently being analyzed, and the final results are anticipated to be published in December 2024.

## Discussion

### Expected Findings

This RCT explores the effects of dance, music, and meditation on functional mobility, balance, QoL, cognition, mood, anxiety, behavior, and caregiver burden in individuals with PD. To date, there has been no research comprehensively investigating the benefit of dance or music and meditation on the QoL of patients with PD or the caretakers in Asian populations (including Indians). This will be the first study of its kind to be conducted in an Indian setup. It is also to be noted that none of the earlier studies offered the participants the choice to choose a modality of their preference. This will be the first paper that allows the participant to choose from music and dance.

The RCT, including 10 patients with PD, by Duncan et al [13] aimed to examine the effects of a 2-year, community-based dance class on disease severity and functional mobility in patients with PD. Assessments at baseline, 12 months, and 24 months showed that the intervention group had lower scores on the Movement Disorder Society-UPDRS III, Mini Balance Evaluation Systems Test, and other measures than the control group. The study concluded that participating in community-based dance classes over 2 years improved motor and nonmotor symptom severity, activities of daily living, and balance in individuals with PD [13].

The recent study by Hashimoto et al [46] involved 46 patients with mild to moderate PD who participated in a 12-week intervention. The patients were divided into a dance group, a PD exercise group, and a nonintervention group. The primary outcome measures included the TUG and BBT for motor assessment, the Frontal Assessment Battery at the bedside and Mental Rotation Task to assess cognitive function, the Apathy Scale and Self-rating Depression Scale to assess mental symptoms, and the UPDRS for general assessment. The results showed that the dance group exhibited significant improvements in all the outcome measures, highlighting dance’s positive impact on the mental well-being, self-esteem, and social engagement of those with PD [46]. The guided meditation component may further contribute to stress reduction and relaxation.

The study by Katlen da Silva et al [12] aimed to evaluate the effects of music-based physical therapy on individuals with PD in terms of muscle strength (Medical Research Council Test and Sitting-Rising Test), cognition (Trail Making Test), muscle strength, balance (BBT), and functional mobility (TUG). It was a controlled, nonrandomized clinical trial with an A-B-A design involving 13 individuals with PD. The results showed that music-based physical therapy helped improve balance and functional mobility in individuals with PD. However, these improvements were not maintained after the therapy was discontinued.

The study by Lihala et al [47] in India examined the impact of dance therapy on cognition, QoL, and motor symptoms in 10 patients with mild-to-moderate PD. The results showed improved cognitive function and QoL, as indicated by increased Montreal Cognitive Assessment scores and decreased PDQ-39 scores [47].

Lee et al [48] examined the effects of virtual reality dance exercises on patients with PD. They found that after 6 weeks of treatment, the experimental group showed significant improvements in BBT (from mean 46.0, SD 1.3 to mean 48.1, SD 3.0); activities of daily living (from mean 87.9, SD 1.4 to mean 91.1, SD 3.0); and Beck Depression Inventory (from mean 20.4, SD 0.9 to mean 18.2, SD 2.0) compared to the control group, highlighting a positive impact on these aspects for patients with PD [48].

The studies mentioned above highlight that dance, music, and mindfulness have improved motor and nonmotor symptoms, activities of daily living, balance, cognitive function, and QoL in patients with PD.

### Limitations and Future Implications

However, the study might be subject to some limitations. The 2 limitations to consider are the small sample size and the short duration of the study. A 6-month timeframe may not be sufficient to observe changes in nonmotor symptoms. Future larger, longitudinal RCTs are warranted to verify results. Motor and nonmotor symptoms of PD such as motor disability, gait and balance difficulties, speech disability, and pain are likely to hinder participation in activities such as dance and music. To compensate for this, each session will be customized according to the participants’ needs and abilities. Additionally, the results might be confounded by factors such as changes in medication or differences in baseline medication taken by the patient. Therefore, any changes made to lifestyle and medication over the course of the study will be constantly monitored. This paper will build upon previous research and delve into the effectiveness of non-pharmaceutical therapies in possibly delaying the progression of PD.

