## Methods

### Study Design

The study is a single-blinded, longitudinal, randomized controlled trial (RCT) that will take place over a 6-month time period at Jaslok Hospital and Research Center, Mumbai, India. Participants will be randomly allocated into 2 groups: the control and intervention groups, having 15 participants in each arm. The intervention group will be further divided into dance or music as per the participant’s choice. The CONSORT (Consolidated Standards of Reporting Trial) flowchart summarizes the enrollment and allocation of the participants (Figure 1).

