### Assessments

All assessments will be conducted during the “on phase,” that is, during the phase when the PD medication is in effect. The outcomes will be assessed by a specialist nurse, a neuro-consultant, and a consultant psychologist. The neuro-consultant is a functional neurosurgeon with pioneering work in this field and more than 30 years of experience in movement disorder surgeries. The specialist nurse has been involved in the treatment of movement disorder patients for more than 26 years and is a certified UPDRS assessor. For the reassessments, the marker who conducted the initial assessment will conduct subsequent assessments.

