All participants will be instructed to follow their daily routine and normal medication schedule. They will be instructed to keep the program coordinator informed if they make any significant changes to their treatment or their medication dosage or schedule. The participants in the intervention group will be asked to commit to the program and to take part in music or dance and meditation sessions thrice, weekly, for 6 months. On a weekly basis, patients should attend at least 1 session in physical presence, while the other sessions will be monitored through videoconferencing and home-based logs.

The patients will also be provided with the recordings of videos with instructions and a breakdown of each activity taught during the face-to-face sessions, making it easier for the participants to practice at home. A complete audio of the guided meditation schedule will be shared with the patients as well. The patients will be instructed to maintain an activity logbook documenting their adherence to home-based practice. Class attendance will be monitored and documented.

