### Data Analysis

IBM SPSS software will be used for the statistical analysis. Descriptive statistics will summarize the demographics, health conditions, and clinical outcomes at all 3 time points. Categorical variables including the Likert rating scales will be expressed in percentages and frequencies. The median and mode will also be ascertained for these data. Additionally, chi-square tests will be conducted, and *P* values will be ascertained to decipher the difference between the 2 groups against each outcome variable throughout the 3 time points.

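### Baseline medication is named as a possible confounder, but neither the stated remedy nor the stated test can deal with a baseline difference

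*Protocol article*

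**What the plan says.** Under Limitations and Future Implications, the protocol article names two separate medication risks: "the results might be confounded by factors such as changes in medication or differences in baseline medication taken by the patient". The next sentence draws one conclusion from both: "Therefore, any changes made to lifestyle and medication over the course of the study will be constantly monitored". The Intervention Group section points the same way. It asks participants to "keep the program coordinator informed if they make any significant changes to their treatment or their medication dosage or schedule", which again concerns only what happens after entry.

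The between-group analysis is given under Data Analysis, where "chi-square tests will be conducted" for the two groups on each outcome variable. No covariate is mentioned. The Randomization section states no stratification factor, and the eligibility criteria set no condition on medication.

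On the state in which patients are measured, the Assessments section says: "All assessments will be conducted during the “on phase,” that is, during the phase when the PD medication is in effect". The primary outcomes, UPDRS I-III and PDQ-39, are therefore recorded with each patient's medication acting.

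**The concern.** The remedy does not match the risk. Recording later changes may help in interpreting the first named risk, but it cannot act on the second, which exists before any monitoring begins. The stated test cannot close the gap either, because a plain chi-square test of arm against outcome has no place for a baseline covariate.

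Baseline medication is a plausible prognostic factor here because scoring is done on medication. Two patients with the same on-phase score may be on different regimens, so the baseline score need not carry all the information in the medication. That is reasoning from the assessment rule; the article does not state it. At stake is how far the primary comparison can be moved by a chance difference that the authors themselves list as a threat, in a trial with about 14 patients per arm.

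**Working it through.** The article gives no standard deviation, effect size, correlation or sample-size calculation, so there is no design figure to reproduce. The completer percentages do check: 15/28 = 53.6% and 13/28 = 46.4%, which round to the printed 54% and 46%.

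**Inputs**
- Planned allocation, Study Design: "the control and intervention groups, having 15 participants in each arm".
- Completers, Results: 28 of 30, with 15 in the intervention arm and 13 in the control arm.
- Assumed: partial correlation r between baseline medication and the 6-month score, given the baseline score, of 0.2 to 0.4.

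**1. How often a sizeable chance imbalance occurs.** The SD of a standardised baseline difference is sqrt(1/n1 + 1/n2). Two-sided normal tail areas follow.

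| Arms | SD of difference | P(at least 0.5 SD) |
|---|---|---|
| 15 v 15 | sqrt(1/15 + 1/15) = 0.365 | 17% |
| 15 v 13 | sqrt(1/15 + 1/13) = 0.379 | 19% |

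For 15 v 13, the chance of at least 0.3 SD is 43%, and of more than 0.75 SD is 4.8%.

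**2. What a 0.5 SD imbalance does to the estimate.** Taking the imbalance to be in the part of medication not explained by the baseline score, shift = 0.5 × r, in residual SD units of the outcome:
- r = 0.2: 0.10
- r = 0.3: 0.15
- r = 0.4: 0.20

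Against a standard error of 0.379 in the same units, this is 0.10/0.379 = 0.26 to 0.20/0.379 = 0.53 of one standard error.

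**3. What adjustment does to precision.** A model with arm and baseline score leaves 28 − 3 = 25 degrees of freedom; one more covariate leaves 24. Variance ratio = (1 − r²) × 25/24:
- r = 0.2: 0.96 × 25/24 = 1.00
- r = 0.3: 0.91 × 25/24 = 0.948
- r = 0.4: 0.84 × 25/24 = 0.875

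The gain is therefore 0% to 12.5% of the variance.

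**4. Error rates by simulation.** 20,000 null trials of 15 v 13 were simulated for each correlation, with a t-test standing in for any unadjusted comparison. The correlations are assumed and are not conditional on a baseline score.

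| r | Unadjusted, all trials | Unadjusted, imbalance above 0.5 SD | Adjusted, imbalance above 0.5 SD |
|---|---|---|---|
| 0.3 | 4.9% | 7.4% | 5.0% |
| 0.5 | 5.3% | 11.4% | 5.6% |
| 0.7 | 5.0% | 16.6% | 4.8% |

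Overall error is kept; the inflation appears only in trials where the imbalance is large. Only r = 0.3 lies in the range used in steps 2 and 3. The two lower rows describe a stronger relation than would be expected once the baseline score is in the model.

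**The case against.** The strongest reply is that allocation is randomised. A baseline medication difference is then chance, not systematic confounding, and a valid unadjusted test already allows for it. This stands: overall type I error stays near 5%. A reader might infer from the article's own word, confounded, that the primary result would be invalid, or that no programme effect could be told apart from a medication difference. The documents do not support that. About four trials in five would have an imbalance below 0.5 SD, and the shift at 0.5 SD is roughly a quarter to a half of one standard error. One caution is that the randomisation argument strictly covers the 30 allocated. If 15 were allocated per arm as planned, both losses were in the control arm.

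Second, covariates and baseline-table contents are commonly left to an analysis plan, and none is shown. This stands in part. One cannot infer that baseline medication was not recorded or will not be tabulated. But the article itself states the risk, the remedy and the test, and these do not fit together.

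Third, the gain beyond the baseline score is modest and rests on assumed correlations. This also stands: at r = 0.2 adjustment only breaks even on variance. Further, the stated analysis contains no baseline-adjusted model, so a medication covariate cannot simply be added; the comparison has to be replaced first.

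Fourth, no section mentions an entry medication record or a dose summary. The fix must therefore be conditional on those data existing.

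**Conclusion.** The point holds in a limited form. The article names baseline medication differences as a possible confounder, offers a remedy that cannot reach them, and states a test that takes no covariate. The consequence is conditional bias when an imbalance happens to occur, together with a modest loss of precision. It is not a systematic bias or a breakdown of error control.

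The chance of a 0.5 SD imbalance depends only on the arm sizes and hardly changes between planned and completing numbers. The resulting shift and the precision gain depend on the assumed partial correlation of 0.2 to 0.4, which the article neither supports nor contradicts. Adjustment is worthwhile because it is inexpensive and deals with a factor the authors chose to name; the expected gain is not large.

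**What to change.** - **Data Analysis:** replace the chi-square comparison of UPDRS I-III and PDQ-39 with a linear model of the 6-month score on arm and baseline score. Add one summary of baseline antiparkinsonian medication, for example a levodopa-equivalent dose, if entry medication was recorded. With 28 completers, add no further covariates.
- **Baseline table:** show that medication summary by arm.
- **Limitations:** claim monitoring only for in-study changes, and name the covariate as the answer to baseline differences. If entry medication was not recorded, say that this limitation remains.
- **In-study medication changes:** report them by arm, but do not adjust for them, because they arise after allocation.
- **Timing:** data collection ended in February 2024 and the article says analysis is in progress. Fix the model before group comparisons are seen; otherwise label it post hoc.

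The cost is one degree of freedom of about 25, one row in the baseline table and the work of extracting entry medication data.

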### Conclusions

This study aims to provide significant insights into the effectiveness of dance or music and education in improving the QoL and slowing the progression of PD. The findings are expected to support the use of nonpharmaceutical therapies as a complementary approach to managing PD, offering potential benefits to both patients and their caregivers.

## Appendix

Multimedia Appendix 1 A consent form.

## Abbreviations

BBT: Berg Balance Test
CONSORT: Consolidated Standards of Reporting Trial
PD: Parkinson disease
PDQ-39: Parkinson’s Disease Questionnaire-39
QoL: quality of life
RCT: randomized controlled trial
TUG: timed up and go
UPDRS: Unified Parkinson’s Disease Rating Scale
